### Sample Size

We calculated the sample size needed with the method described by Hussey and Hughes [35]. Based on the previous study, we expect a hazard ratio of 1.5 on the primary outcome full sustainable RTW. To achieve a power of 0.8 with a two-tailed alpha of .05, and taking into account a dropout rate of 10%, a total of 212 patients will be needed when using the log-rank test.

With an intracluster correlation of .05, 9 clusters, and 10 time periods, the design effect is calculated to be 2.14 [35]. By multiplying the design effect by the sample size without a correction for a stepped wedge design, a sample size of 454 women is needed. Assuming that all of the hospitals will include the same amount of participants, each hospital should include approximately 50 patients (5 patients per time period per hospital).

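### The design effect of 2.14 belongs to about 2.4 patients per hospital-period; at the planned 5 it is 2.38, and 454 women give about 76% power, not 80%

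*Protocol article*

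**What the plan says.** The Sample Size section works in three steps.

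1. It expects a hazard ratio of 1.5 for full sustainable return to work (RTW). "To achieve a power of 0.8 with a two-tailed alpha of .05", and with 10% dropout, "a total of 212 patients will be needed when using the log-rank test".
2. It names the Hussey-Hughes stepped-wedge method and reports: "With an intracluster correlation of .05, 9 clusters, and 10 time periods, the design effect is calculated to be 2.14".
3. It multiplies the two figures and concludes that "a sample size of 454 women is needed". With equal recruitment, "each hospital should include approximately 50 patients (5 patients per time period per hospital").

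The section does not say what number of patients per hospital-period was used to obtain 2.14. The Trial Design section fixes the rollout: all hospitals are in the control phase in the first period, and one hospital crosses over at the start of each of periods 2 to 10. The Statistical Analyses section includes time period as a covariate in the adjusted Cox model.

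**The concern.** The stepped-wedge design effect is a function of four quantities: the intracluster correlation, the number of clusters, the number of periods and the number of patients per cluster-period. It rises with the last of these when the correlation is .05. The section gives the first three, a design effect, and then a cell size of 5, and these five figures do not agree with each other.

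This calculation is the only justification given for the size of the trial and for the power on the primary outcome. If the design effect is too low, the 80% is not delivered under the plan's own assumptions, and a null result would be judged against a power the trial did not have.

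**Working it through.** **Inputs, all from the protocol article.** Hazard ratio 1.5, power 0.80, two-sided alpha .05, dropout 10%, intracluster correlation ρ = .05, 9 hospitals, 10 periods, 454 women, 5 per hospital-period (Sample Size); one all-control period, then one hospital crossing per period (Trial Design). Equal cell sizes are assumed, as the plan does. Then 9 + 8 + … + 1 = 45 of the 90 hospital-periods are intervention, so allocation is 1:1 overall.

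**Step 1: the unadjusted sample.** Schoenfeld events = 4(1.960 + 0.8416)² / (ln 1.5)² = 190.97. Dividing by 0.9 gives 212.2. The stated 212 reproduces. Every woman who does not drop out is counted as an event.

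**Step 2: the multiplication.** 212 × 2.14 = 453.7, so 454 reproduces. With a design effect of 2.14, 454 × 0.9 / 2.14 = 190.9 effective events, and power is 80.0%. Everything therefore turns on the 2.14.

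**Step 3: the design effect.** For k = 9 steps, b = 1 baseline period, t = 1 period per step and n patients per hospital-period, relative to an individually randomised 1:1 trial of the same total size:

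DE = [1 + ρ(ktn + bn − 1)] / [1 + ρ(ktn/2 + bn − 1)] × 3(1 − ρ) / [2t(k − 1/k)] × (b + kt)

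With the plan's values this reduces to DE(n) = 1.6031 × (0.95 + 0.5n) / (0.95 + 0.275n). Direct computation of the generalised least squares variance from the Hussey-Hughes model with period effects gives the same values.

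| Patients per hospital-period | Design effect |
|---|---|
| 2.356 (212/90) | 2.135 |
| 2.40 | 2.141 |
| 4.5 (5 less 10% dropout) | 2.345 |
| 5 (planned) | 2.379 |
| 5.044 (454/90) | 2.382 |

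The planned case in full: 1.6031 × (0.95 + 2.5) / (0.95 + 1.375) = 1.6031 × 3.45 / 2.325 = 2.379. Setting DE(n) = 2.14 gives n = 2.39. That is close to the unadjusted sample spread over the 90 cells.

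**Step 4: other readings at 5 per cell and ρ = .05.** Dropping the first or the last period gives 2.23. Ten clusters and 11 periods give 2.39. No period effects gives 1.18. A parallel cluster design with about 50 per hospital gives 3.47. None gives 2.14.

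**Step 5: power at 454 women.** Effective events = 454 × 0.9 / 2.382 = 171.5. Power = Φ(√(171.5/4) × ln 1.5 − 1.96) = Φ(0.695) = 75.7%. With the design effect at 4.5 analysed patients per cell (2.345), power is 76.3%. The hazard ratio detectable with 80% power is exp(2.8016 / √(171.5/4)) = 1.53.

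**Step 6: sample size for 80% power at 1.5.** 212 × 2.379 = 504. Since a larger total enlarges the cells, the self-consistent solution of N = 212 × DE(N/90) is N = 513, with 5.7 per cell, 57 per hospital and a design effect of 2.42. Both are above 454, by 11% and 13%.

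**Step 7: sensitivity to the event share (assumption).** The document gives no share of women without sustained RTW by 12 months. If 5% to 10% of those retained have no event, the effective events fall in proportion and power is 73.5% to 71.2%. The conclusion does not depend on this.

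**The case against.** The strongest reply is that the source of the slip is not shown. An intracluster correlation of .02 with 5 per cell also gives 2.14 (2.140). The article never says which cell size went into the calculation, and 212/90 gives 2.135, which sits on the rounding boundary. If .02 was used and .05 was misreported, 454 women would give about 80% power, and restating the power as 76% would be wrong. This is a fair limit on any account of the cause: that the unadjusted sample was used for the cell size is an inference from the numbers. It does not rescue the text, because the stated correlation is .05. On either reading the section contains a wrong figure.

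A second reply is that 4 points lie inside the uncertainty of the calculation. The correlation is given without a source in this section. Over an illustrative range of .01 to .10, at 4.54 analysed patients per cell, power runs from 84% to 75%. The method also applies a design effect for a continuous outcome to log-rank events, while the planned analysis is a Cox model with a gamma random effect. Both remarks are true. They are reasons to read 75.7% as about 76%. They do not support 80%, because the comparison uses the plan's own method and inputs throughout.

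Thirdly, the confidence interval for the hazard ratio will matter more than nominal power in reading a null result. That stands and limits the consequence, but it does not make the stated power correct.

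**Conclusion.** The concern holds. At the stated correlation, numbers of hospitals and periods, and cell size, the design effect is 2.38, so the stated 2.14 is too low. The 454 women give about 76% power for a hazard ratio of 1.5 (type II error about 24% instead of 20%), or 80% power for a hazard ratio of 1.53. The loss is moderate, and the estimand, randomisation and analysis are unaffected. The result rests on equal cell sizes, 10% dropout, an event in every retained woman, and the plan's own use of the Hussey-Hughes design effect on a log-rank event count. How 2.14 arose cannot be settled from the article, and the verdict does not need it.

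**What to change.** Keep 454 women and correct the figures in the Sample Size section:

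- State the cell size used, and give the design effect as 2.38 at 5 patients per hospital-period.
- State the power for a hazard ratio of 1.5 as about 76%, or equivalently 80% power for a hazard ratio of 1.53.
- Show how power depends on the share of women with an observed RTW event.

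If the authors' working shows that a correlation other than .05 was used, that figure should be corrected and justified, and the power reported to match.

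The cost is wording and a less favourable stated power. No extra patients and no design change are needed. The article reports that data cleaning and analysis had not begun at submission, so the correction can still be made before results are known.

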### Statistical Analyses

#### Effect Evaluation

All further described analyses will be performed at the patient level, according to the intention-to-treat principle. In addition, for all tests, a two-tailed significance level of *P*≤.05 will be considered statistically significant. The statistical software packages that will be used include SPSS (version 16.0) and STATA (version 11.2).

The baseline characteristics will be summarized using descriptive statistics, and compared between the experimental and control group to verify prognostic comparability. In case of coincidental and meaningful differences, these variables will be used as covariates in the further described models.

For the primary outcome, the duration of sick leave until full sustainable RTW, Cox regression analyses will be used to investigate the intervention effect. Both the crude and adjusted analyses will be performed. In the adjusted analyses, the following variables will be used as covariates: (1) hospital, to adjust for clustering (random gamma effect); (2) type of surgery performed; (3) time period, to adjust for naturally occurring changes over time irrespective of the intervention; and (4) optionally, (time period) x (intervention) interaction term, to adjust for time effects (the longer the care program is implemented, the more effective it might be).

The differences in secondary outcomes will be assessed using generalized linear longitudinal mixed models. All of the available measurements (2 weeks, 6 weeks, 12 weeks, 26 weeks, and 52 weeks) will be used, and the baseline scores will be used as covariates, as well as the hospital and the type of surgery (random effect).

To assess whether protocol deviations caused bias, a per protocol analysis will be performed, and the results will be compared to the intention-to-treat analyses. In addition, several subgroup analyses will be performed. The predefined subgroups will be: (1) hysterectomy (TAH, VH, TLH); (2) minimally invasive hysterectomy (VH, TLH); (3) abdominal hysterectomy only; and (4) laparoscopic adnexal surgery only.

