##### Occupational Intervention

The occupational intervention is developed to provide additional guidance to those patients at risk for prolonged sick leave. The occupational intervention will be delivered by a group of six independent OPs, who will be trained as RTW coordinators before the start of the trial. There are two types of consultations: (1) a preoperative, and (2) a postoperative consultation. All consultations will be delivered by telephone, unless the OP and the patient decide together otherwise.

The patients who have an inadequate expectation about their own recovery (longer than 3 weeks for LAS, longer than 6 weeks for VH/TLH, or longer than 8 weeks for TAH), or have a low intention to resume work activities while still recovering, are offered a preoperative consultation, as expectations about RTW and intention to resume work have been identified as two predictors for RTW in recent studies [10,40,41]. During the preoperative consultation, the OP explains the importance of a prosperous recovery in terms of improving quality of life and preventing long term sickness. In addition, the OP tries to identify and—if necessary—alter attitudes and (irrational) beliefs about recovery.

The patients who exceed 5 weeks of sick leave receive a postoperative consultation, during which, the OP assesses the underlying mechanism for the delayed recovery. The OP gives advice to improve the reintegration process. Moreover, as a RTW coordinator, the OP has an excellent position to communicate with the patient’s gynecologist, GP, OP, and employer, if necessary, and of course, with the consent of the patient, stimulating an integrated care approach. In addition, the OP has the possibility to initiate a participatory workplace intervention, aimed at finding consensus between the patient and her employer concerning solutions for identified obstacles for RTW with the help of an occupational therapist (OT) [42,43].

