#### Prognostic Factors

Before surgery, data about potential prognostic factors will be collected. In case of coincidental and meaningful differences, analyses will be adjusted for the following characteristics: (1) sociodemographic data such as age, education level, and ethnicity; (2) personal factors such as expectation, motivation, and intention toward RTW, duration of sick leave in the past 3 months; and (3) work related factors such as physical workload and potential work related psychosocial factors, assessed by the Dutch Musculoskeletal Questionnaire (DMQ) [52] and the Job Content Questionnaire (JCQ) [53].

In case of an unequal distribution of severe complications (defined as: wound enlargement with more than 8cm or repeat surgery within 2 weeks), between the two study arms, the analyses will be adjusted for these surgery-related characteristics as well.

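### Baseline prognostic factors, including return-to-work expectation and intention, enter the models only if an imbalance is seen, so the hazard ratio being estimated depends on chance and power is forgone

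*Protocol article*

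**What the plan says.** The Effect Evaluation section says that baseline characteristics will be summarised and "compared between the experimental and control group to verify prognostic comparability". It continues: "In case of coincidental and meaningful differences, these variables will be used as covariates in the further described models". The Prognostic Factors section states the same rule for a named list: "In case of coincidental and meaningful differences, analyses will be adjusted for the following characteristics". That list covers sociodemographic data, work-related factors such as physical workload, and "personal factors such as expectation, motivation, and intention toward RTW, duration of sick leave in the past 3 months".

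The Occupational Intervention section gives the reason for offering a preoperative consultation: "expectations about RTW and intention to resume work have been identified as two predictors for RTW in recent studies". Two of the conditional candidates are therefore ones that the article itself identifies as predictors of the primary outcome.

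Some covariates do not depend on balance. For the primary outcome: "In the adjusted analyses, the following variables will be used as covariates: (1) hospital, to adjust for clustering (random gamma effect); (2) type of surgery", followed by time period and an optional period-by-intervention term. The secondary models always include the baseline score, hospital and type of surgery. For the primary outcome, "Both the crude and adjusted analyses will be performed"; the article does not say which of the two carries the conclusion.

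**The concern.** A rule triggered by imbalance answers the wrong question. In a randomised comparison, the gain from adjusting for a baseline variable comes from how well it predicts the outcome, and that gain is there when the arms are balanced. Under this rule a good predictor is left out precisely when the arms happen to look alike.

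For a Cox model there is a second consequence. The HR is non-collapsible: leaving out a prognostic covariate moves the treatment HR toward 1 even with perfect balance. Whether the trial reports an HR conditional on RTW expectation, or one averaged over it, would then depend on a chance difference at baseline. Two trials with the same program effect would be estimating different quantities.

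At stake are a primary estimand that is not fixed in advance, and power that variables already collected could supply.

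**Working it through.** **Inputs from the Sample Size section.** HR 1.5, power 0.8, two-sided alpha .05, dropout 10%, 212 patients before the design effect, design effect 2.14, total 454.

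**Inputs that are assumed, because the documents give no figures.** One standardised baseline predictor with SD 0.3, 0.5 or 0.7 on the log-hazard (HR per SD e^0.3 = 1.35, e^0.5 = 1.65, e^0.7 = 2.01). *Meaningful* is read as a standardised difference above 0.1 or above 0.2.

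**1. Reproduce the plan's figures.** Events = 4(1.960 + 0.842)² / (ln 1.5)² = 191.0. Divided by 0.9 this is 212.2, stated as 212. Then 212 × 2.14 = 453.7, stated as 454. The figures reproduce.

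**2. Effective size.** 454 / 2.14 = 212.1; × 0.9 = 190.9, so 191 individually randomised equivalents.

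**3. How often would a predictor enter by chance?** The layout puts 1 + 2 + ... + 9 = 45 of 90 hospital-periods under intervention, so the arms are about equal. The standard error of a standardised difference is then √(4/n).

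| n | Standard error | Chance of exceeding 0.1 | Chance of exceeding 0.2 |
|---|---|---|---|
| 191 | 0.145 | 49% | 17% |
| 454 | 0.094 | 29% | 3% |

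With P<.05 as the trigger, the chance is 5% by construction. A predictor is left out more often than not under every reading tried. The simulation in step 4 uses n = 191, where the trigger fires more often than it would among 454 women, so on this point it is generous to the rule.

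**4. Effect of the rule itself.** Simulated Cox analyses with 191 patients and a true conditional HR of 1.5. Ranges in the triggered columns run over the two thresholds.

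| Predictor SD | Triggered: mean HR | Triggered: power | Always adjusted: mean HR | Always adjusted: power |
|---|---|---|---|---|
| 0.3 | 1.48-1.50 | 76-77% | 1.50-1.52 | 77-79% |
| 0.5 | 1.43-1.46 | 66-71% | 1.50-1.52 | 77-79% |
| 0.7 | 1.39-1.43 | 57-65% | 1.50-1.52 | 77-79% |

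The always-adjusted ranges hold across all three strengths. Subtracting, the loss is at most about 3 points for SD 0.3, about 6 to 13 for 0.5 and about 12 to 22 for 0.7. These are simulated values, good to a few points.

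**5. Type I error.** In a separate simulation (192 events, covariate HR 1.5 to 2.5 per SD, triggers P<.05, 0.2 and 0.1), the rule rejected in 3.1% to 4.6% of trials with no true effect. It is slightly conservative.

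**6. Does the loss survive hospital and period adjustment?** A simulation of the layout used 9 hospitals, 10 periods and 5 patients per cell, with hospital and period as fixed effects, 10% dropout and 400 replicates. Without the predictor, HR was 1.47, 1.43 and 1.39 and power 61%, 54% and 50%. With it, HR was 1.52-1.53 and power 65-68%. This contrasts never with always adjusting, so it bounds the rule's loss from above; with 400 replicates each power has a standard error of up to √(0.25/400) = 2.5 points. The loss does not vanish. The trigger fired in 25-27% of trials at 0.1 and 2-5% at 0.2.

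**7. If 1.5 is the marginal HR.** A run with 174 patients, somewhat fewer than the 191 above and used only for the pattern, gave unadjusted power of 74-75% at all three strengths. Adjustment raised it to 82%, 88% and 92%.

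**The case against.** **The planned HR may be marginal.** The Sample Size section ties HR 1.5 to the log-rank test, which is an unadjusted comparison. If 1.5 is marginal, the imbalance rule causes no shortfall against the plan; it only forgoes a gain. This stands, and the size must be stated both ways.

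**The size depends on two unknowns.** Predictor strength and the threshold for *meaningful* are both assumed. An article may leave a numeric threshold to the full plan, so its absence carries little weight. The finding is the stated rule itself, which is a poor one at any of the thresholds tried.

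**Stronger readings that a reader might infer, and that the documents do not support:**
- *No covariates are fixed in advance.* Hospital, type of surgery and period are fixed in the adjusted primary model, and baseline scores in the secondary models. Surgery type is plausibly prognostic, since the expectation limits in the Occupational Intervention section differ by procedure.
- *Strong predictors are ignored.* The article says predictors, not strong ones, and they can enter if an imbalance appears.
- *Power drops as far as a never-adjusted model implies.* The rule adjusts in some trials, so its loss lies between never and always adjusting.
- *The result is biased or the false-positive rate is raised.* Non-collapsibility changes the quantity estimated; under the null the rule was conservative.
- *The analyst will choose covariates knowing the arm.* Hospital and period together determine the arm in this design, but the Blinding section says the analysis will be blind under study codes, and does not say whether those two variables are masked. This is possible, not shown.

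**Conclusion.** The point holds as one of efficiency and of a stable estimand. The rule is stated twice, and it makes two variables that the article itself calls predictors of RTW conditional on chance imbalance. On an assumed conditional HR of 1.5, the power loss ranges from negligible (SD 0.3) to about 12 to 22 points (SD 0.7), and the mean HR falls to as low as 1.39. On a marginal HR of 1.5, planned power is intact and the loss is the added power that adjustment would bring. In both cases which HR is estimated is left to chance. These sizes rest on a single predictor independent of the covariates already fixed, and the main simulation replaces clustering and period effects by an effective sample size. The change is worth making because it is nearly free.

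**What to change.** Delete the imbalance rule for baseline factors in both sections. Before analysis starts, fix a short covariate set from the Prognostic Factors list: at least RTW expectation and RTW intention, plus age, sick leave in the past 3 months and physical workload. Enter it in the adjusted primary model whatever the balance, alongside hospital, surgery type and period, and name that model as primary, with the crude model as supportive. Keep the baseline table descriptive.

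The cost is a few degrees of freedom and a short text change. All these variables are collected before surgery, and the Randomization section says allocation is disclosed only after the first questionnaire. N stays at 454. The Results section states that neither data cleaning nor analysis had begun at submission, so the set can still be fixed in advance. The separate conditional rule for severe complications is not covered by this change.

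### The primary outcome gets both a crude and an adjusted Cox test at .05 with neither named as deciding, and the crude one rejects a true null about 12% of the time at the plan's ICC

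*Protocol article*

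**What the plan says.** Effect Evaluation (under Statistical Analyses) assigns Cox regression to the primary outcome and continues: "Both the crude and adjusted analyses will be performed". Four terms are then listed, for the adjusted analyses only:

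- hospital, as a gamma random effect to allow for clustering;
- type of surgery;
- "time period, to adjust for naturally occurring changes over time irrespective of the intervention";
- optionally, a period-by-intervention interaction, with no rule for when it is included.

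The same section sets "for all tests, a two-tailed significance level of" P≤.05. No sentence ranks the crude and adjusted models.

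Sample Size starts from "we expect a hazard ratio of 1.5 on the primary outcome full sustainable RTW", inflates for a stepped wedge ("With an intracluster correlation of .05, 9 clusters, and 10 time periods, the design effect is calculated to be 2.14") and concludes that "a sample size of 454 women is needed".

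**The concern.** One primary outcome yields at least two intervention hazard ratios, each judged at the same threshold, and a reader cannot tell which decides whether the program works. This would matter less if the crude model were merely less precise, but in this rollout it is not a valid test. Hospitals contribute very different shares of their patients to the two conditions, so differences between hospitals enter the crude hazard ratio. Intervention patients also come later in calendar time, so any drift in RTW enters too. The protocol recognises both threats, since it gives them as its reasons for including hospital and period in the adjusted model. If the two models disagree, nothing in the text prevents a significant crude result from being presented as the trial's finding.

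**Working it through.** **The plan's own figure.** Inputs from Sample Size: "To achieve a power of 0.8 with a two-tailed alpha of .05", hazard ratio 1.5, 10% dropout, design effect 2.14.

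- Events = (1.960 + 0.842)² / (0.25 × (ln 1.5)²) = 190.97.
- Patients = 190.97 / 0.9 = 212.2, so 212.
- 212 × 2.14 = 453.7, so 454.

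The plan's 212 and 454 follow from its stated inputs. The total therefore rests on a clustered stepped-wedge calculation, not on a crude test.

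**Layout.** From Trial Design and Sample Size: 9 hospitals, 10 two-month periods, one hospital switching per step, 5 patients per hospital-period. Hospital i has i control and 10 − i intervention periods. Each condition has 45 hospital-periods, or 225 patients. Hospitals place between 90% (i = 1) and 10% (i = 9) of their patients in the intervention condition.

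**Calendar imbalance.** Mean period of control cells = 165/45 = 3.67; of intervention cells = 330/45 = 7.33. The difference is 3.67 periods, or about 7 months.

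**Crude test, ICC as a share of outcome variance** (the sense in which a design-effect formula uses it; no calendar trend; total variance set to 1):

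- Weight of hospital i in the crude contrast = (10 − 2i)/45.
- Sum of squared weights = (64 + 36 + 16 + 4 + 0 + 4 + 16 + 36 + 64)/2025 = 240/2025 = 0.1185.
- Variance assumed by the crude test = 2/225 = 0.00889.
- True variance = 0.05 × 0.1185 + 0.95 × 0.00889 = 0.00593 + 0.00844 = 0.01437.
- Inflation = 0.01437/0.00889 = 1.62.
- Rejection rate = 2(1 − Φ(1.96/√1.62)) = 12.3%. Simulation of this linear case gives 12.4%.

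**Crude Cox or log-rank test under other readings of the ICC** (no calendar trend). The protocol gives no scale, so the hospital variance θ on the log-hazard scale is an assumption. Formula: inflation = 1 + 0.1185 θ/(4/events), here with 405 events (90% of 450).

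| Reading of ICC .05 | θ | By formula | Simulated |
|---|---|---|---|
| θ = .05 | 0.050 | 12.1% | 11–12% |
| θ/(θ + π²/6) = .05 | 0.0866 | 17.0% | 15–17% |
| Kendall's tau = .05 | 0.105 | 19.3% | 17–18% |

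With no hospital variation, the simulated crude test rejects in about 5%, as it should. The excess in the table is therefore due to hospital alone.

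**Adding a calendar trend** (assumed; the protocol gives none). With a 1.2-fold rise in the RTW hazard over the trial, the crude test rejects in 18.0% (θ = .05) to 20.3% (θ = .0866). It rejects in 12.4% even with no hospital variation. With a 1.5-fold rise, as large as the planned effect itself, the rate is 38–39%.

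**Adjusted model under the same null, no trend.** 5.1% for a linear mixed model with known variances; 5.4–6.1% for a Cox model with fixed hospital and period effects, a stand-in for the gamma frailty. It is close to nominal.

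**The case against.** The strongest reply is that the adjusted model is plainly the intended one. The trial is sized with a stepped-wedge design effect, and the protocol explains why hospital and period are in the model. Showing crude beside adjusted results is ordinary practice, and a formal ranking might sit in a fuller document. It can be added that the Introduction names the economic evaluation as the primary objective, so policy would not turn on this P value alone.

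Much of this stands. The intention can be inferred, and the adjusted test has roughly its nominal error rate. But the article does not merely leave a detail open. It puts two tests of its one primary outcome under a single significance rule, and one of them is invalid in this design. Nor is the adjusted model a single model while the interaction remains optional. RTW is still the named primary outcome, and the one on which the trial was sized.

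Three stronger readings are tempting, and the document does not support them:

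- *The crude error rate is 17% at the plan's ICC, because hospital and period are ignored.* That figure needs a conversion to the log-hazard scale that the protocol does not state. It also arises with no calendar trend, so period contributes nothing to it.
- *The trial's false-positive rate is 15–21%.* This is the rate at which at least one of the two tests is significant with no trend. The plan never says that either result suffices for a claim.
- *The trend figures are the trial's error rates.* They show sensitivity to assumed trends only.

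**Conclusion.** The point holds as a failure to name the deciding analysis, made consequential by an invalid crude test. At the plan's ICC of .05 read as a variance share, the crude test rejects a true null about 12% of the time; the simulated range across scales of the ICC is about 11–18%. On every reading checked, that is at least double the stated 5%. These figures assume equal recruitment of 5 per hospital-period, the rollout as described and no calendar trend. A trend would add to them because of the 3.67-period imbalance, by an amount the protocol gives no means of fixing. The adjusted model is not at fault, and the text already leans towards it; what is missing is the statement that it decides.

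**What to change.** In Effect Evaluation, state that the single primary test is the intervention hazard ratio from the Cox model with hospital frailty, type of surgery and time period, at two-sided .05. Keep the optional period-by-intervention term for a secondary analysis, because with it in the model the intervention coefficient is no longer one overall effect. Label the crude model as unadjusted and descriptive, and state that no conclusion on effectiveness rests on it.

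This is a change of wording and needs no new data. The Results section says that data cleaning and analysis had not begun at submission, so it can still be made in advance. The downside is that the crude P value can no longer support a claim.
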